## Abstract

**Background:**

Past trauma and exposure to violence have been related to poor emotion regulation and household violence, which can have persistent mental health effects across generations. The Family Strengthening Intervention for Early Childhood Development (FSI-ECD/called Sugira Muryango in Rwanda) is an evidence-based behavioral home-visiting intervention to promote caregiver mental health, positive parenting practices, and early childhood development among families facing adversity. In Sierra Leone and other lower- and middle-income countries, mobile health (mHealth) technology has the potential to improve health care delivery and health outcomes.

**Objective:**

This study aims to (1) apply a user-centered design to develop and test mHealth tools to improve supervision and fidelity monitoring of community health workers (CHWs) delivering the FSI-ECD and (2) conduct a pilot randomized controlled trial of the FSI-ECD to assess feasibility, acceptability, and preliminary effects on caregiver mental health, emotion regulation, caregiving behaviors, and family violence in high-risk families with children aged 6-36 months in comparison with control families receiving standard care.

**Methods:**

We will recruit and enroll CHWs, supervisors, and families with a child aged 6-36 months from community health clinics in Sierra Leone. CHWs and supervisors will participate in 1 problem analysis focus group and 2 user interface/user experience cycles to provide feedback on mHealth tool prototypes. Families will be randomized to mHealth-supported FSI-ECD or standard maternal and child health services. We will collect quantitative data on caregiver mental health, emotion regulation, caregiving behaviors, and family functioning at baseline, postintervention, and 3-month follow up. We will use a mixed methods approach to explore feasibility and acceptability of mHealth tools and the FSI-ECD. Mixed effects linear modeling will assess FSI-ECD effects on caregiver outcomes. Cost-effectiveness analysis will estimate costs across FSI-ECD versus standard care.

**Results:**

Funding for this study was received from the National Institutes of Mental Health on August 17, 2020. Institutional Review Board approval was received on September 4, 2020. Data collection is projected to begin on December 15, 2020.

**Conclusions:**

This study will provide important data on the feasibility, acceptability, and preliminary efficacy of mHealth-supported delivery of an evidence-based family home-visiting intervention in a postconflict LMIC.

**Trial Registration:**

ClinicalTrials.gov NCT04481399; https://clinicaltrials.gov/ct2/show/NCT04481399.

**International Registered Report Identifier (IRRID):**

PRR1-10.2196/25443

## Introduction

### Background

Exposure to war, trauma, and other humanitarian crises can have persistent mental health effects across generations, including intergenerational violence [1-3]. The World Health Organization (WHO) estimates that 35% of women globally report experiencing intimate partner violence in their lifetime, and 75% of children in lower- and middle-income countries (LMICs) experience some form of violent or psychologically damaging discipline at home. Experiencing or witnessing family violence during early childhood increases risks for poor emotion regulation and other psychological problems, including posttraumatic stress disorder, externalizing and internalizing behavioral difficulties, and school problems. In postconflict Sierra Leone, research on the intergenerational impact of the 11-year civil conflict has shown that exposure to violence is related to poor parent/caregiver mental health and harsh parenting practices, which adversely affect child development [4-8]. The 2017 Sierra Leone Multiple Indicator Cluster Survey found that 85% of children aged 3-4 and 67% of those aged 1-2 experience violent discipline [9]. Given that poor caregiver emotion regulation is related to family violence and poor child development outcomes [4,5], evidence-based interventions focused on enhancing caregiver–child interactions (including father/male caregiver involvement), improving caregiver emotion regulation and mental health, and promoting alternatives to harsh discipline practices are urgently needed.

### Evidence-Based Family Strengthening

In prior research among families facing adversity in Rwanda, we developed and evaluated the Family Strengthening Intervention for Early Childhood Development (FSI-ECD/*Sugira Muryango*), a home-visiting behavioral intervention delivered by lay workers [10,11]. The FSI-ECD targets caregiver emotion regulation and caregiver–child interactions as major mechanisms to prevent the intergenerational transmission of emotional and behavioral difficulties related to past trauma. It has demonstrated effectiveness in improving caregiver emotion regulation, reducing family violence, and promoting healthy child development [7,11]. The FSI-ECD is a promising approach for targeting underlying mechanisms linked to poor child outcomes [6,7]. Vital for low-resource settings, it can be delivered feasibly by lay workers with strong supervision and quality improvement cycles. Given the limited health infrastructure in many LMICs, including Sierra Leone [12,13], behavioral interventions that can be delivered by well-trained and supervised lay workers, such as community health workers (CHWs), are a more viable option for implementation and sustainment of evidence-based practices.

To further address critical shortages in the mental health workforce in LMICs, intervention delivery strategies must innovate. In Sierra Leone, new government leadership is pursuing mobile health (mHealth) strategies as means to address significant health care workforce limitations that plague delivery of evidence-based behavioral interventions to vulnerable families. Mobile technology has the potential to transform health care delivery and improve health outcomes in Sierra Leone and other LMICs by providing training, supervision, and fidelity supports to enhance quality improvement while interventions are scaled out, but it has not been widely applied to mental health and family-based prevention, particularly in Sub-Saharan Africa [8,14,15]. mHealth supervision and fidelity monitoring tools could enhance quality of service delivery and expand the reach of evidence-based mental health services to vulnerable families by generating a rapid feedback loop between supervisors and facilitators unconstrained by geographical distances. However, successful implementation of mHealth tools in Sub-Saharan Africa has been limited by dependence on a reliable network connection and electricity [8]. Although 83% of adult Sierra Leoneans have access to a mobile phone, most lack internet access, particularly in rural areas [16]. In this context, innovative use of battery-powered tablets with offline functions and access to cloud storage are logistically feasible and could help improve delivery quality and supervision of CHWs.

### Study Objectives

The current study aims to (1) pilot a culturally adapted version of the FSI-ECD delivered by CHWs to vulnerable Sierra Leonean families with children aged 6-36 months to assess feasibility, acceptability, and preliminary effects of mHealth-supported delivery of the FSI-ECD on caregiver mental health and emotion regulation, caregiver–child interactions, and family violence in comparison to control families who receive standard care with standard supervision; and (2) develop and pilot innovative and cost-effective mHealth tools to support CHW delivery of the FSI-ECD. Development of mHealth tools will employ a user-centered design approach to design, prototype, and test digital tools that incorporate user feedback from supervisors and CHWs at each stage of development. User-centered design grounds the tool/app development process in the needs and preferences of those who will use the tool to make it more user-friendly, acceptable, and suitable to the real-world needs of the user; it creates a sense of engagement and shared ownership that aids adoption of the innovation [17-19]. We will use participatory methods and best practices in the user interface/user experience (UI/UX) design to engage CHWs and supervisors in the iterative development process to ensure that our mHealth tools and strategies meet their needs, align with local technological capacity and health service priorities, and support sustained evidence-based practice. The objectives are to develop mHealth tools for supervision, fidelity monitoring, and training of CHWs in Sierra Leone and to provide supervisors with quick visual data displays on CHW performance to inform quality improvement cycles. We will also conduct a preliminary cost-effectiveness analysis to assess the economic value of the mHealth-supported delivery of the FSI-ECD versus standard care with standard supervision.

## Methods

### Design

This study is approved by the Boston College Institutional Review Board (reference number 21.006.01; Multimedia Appendix 1) and the Sierra Leone Ethics and Scientific Review Committee. The reporting of the trial follows the Standard Protocol Items: Recommendations for Interventional Trials (SPIRIT) guidelines [20] (Figure 1). This trial is registered with the Clinical Trials Registry maintained by the National Library of Medicine at the National Institutes of Health (Trial ID NCT04481399, registered on July 22, 2020). Any subsequent modifications to the study protocol will be reviewed by the Boston College Institutional Review Board and Sierra Leone Ethics and Scientific Review Committee for approval and then submitted to the Clinical Trials Registry as an amendment.

**Figure 1 figure1:**
[figure not shown]
SPIRIT Schedule of Enrollment, Interventions, and Assessments.

### Overview of Design

We will apply a 5-phase user-centered design approach [21] to develop and test mHealth supervision and fidelity monitoring tools (Figure 2). We will recruit CHWs delivering services to families with children aged 6-36 months (N=6; 3 male/3 female) and CHW supervisors (N=4; 2 male/2 female) to participate in end user focus group discussion sessions. We will hold 3 sessions: an initial problem analysis focus group sessions followed by 2 iterative cycles of UI/UX testing sessions. Problem analysis will seek to understand how CHWs and supervisors might use mHealth tools to enhance fidelity monitoring and supervision and what types of training resources might best support performance. Design of the mHealth tools will be informed by problem analysis findings. Development will test prototyped components of the mHealth tools to integrate audio, replay, visual displays of data, and summary features. UI/UX testing sessions will use Think Aloud Testing Protocols [22], where participants are instructed to “think aloud” while using mHealth tools to illuminate features that are user friendly versus confusing or hard to use. Assessment of strengths and weaknesses of the mHealth tools and the second round of UI/UX testing will inform further refinements prior to the pilot trial. All sessions will be audiotaped, translated, and transcribed. All UI/UX participants will complete a validated usability scale prior to deployment of the mHealth tools [23].

**Figure 2 figure2:**
[figure not shown]
User-centered Design Process for mHealth Tool Development.

We will conduct a pilot randomized controlled trial to evaluate preliminary mental health benefits of the mHealth-supported FSI-ECD among vulnerable families (N=80) with children aged 6-36 months in the Makeni City region of Sierra Leone. Study research assistants will seek informed consent from families, CHWs, and supervisors for their participation. Families will be randomized to receive the FSI-ECD or standard maternal and child health services delivered by a CHW with standard supervision. To minimize contamination risk, we will use randomization rules developed in our prior work in Sierra Leone (eg, geographic information system mapping to ensure nonadjacency of control and FSI-ECD families). The randomization allocation sequence will be generated via computer-generated random number list in REDCap. Study research assistants and data analysts will be blinded to participant assignment and will assign participants to study condition based on the randomization allocation sequence. Different CHWs will provide the FSI-ECD and standard care to minimize contamination risks.

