### Measures

#### FSI-ECD Outcomes

We will collect quantitative data on caregiver mental health and emotion regulation, harsh parenting practices, the home environment, and family functioning at baseline, postintervention, and 3-month follow-up. All quantitative measures have undergone a thorough development, translation, and validation process [26] in a prior randomized controlled trial in Sierra Leone. The following quantitative measures will be used: the DERS (α=.95) [27], WHO Disability Assessment Schedule (α=.91) [28], the Conflict Tactics Scale (α=.72-.86) [29], Hopkins Symptom Checklist (α=.92) [30], and Post-traumatic Stress Disorder Reaction Index (α=.93) [31]. To assess caregiver–child interactions, we will use the Home Observation for Measurement of the Environment (α=.73) [32] and the Observation of Mother–Child Interaction (α=.83) [33]. We will also collect qualitative data at postintervention via key informant interviews with randomly selected caregivers (4 males/4 females) to assess FSI-ECD feasibility, acceptability, and satisfaction.

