## Discussion

### Possible Challenges

There are several potential challenges that may arise during study implementation. In Sierra Leone, many caregivers are involved in employment that requires a high level of daily mobility, such as trade and agriculture. Some caregivers travel across districts, regions, or to neighboring countries for several weeks in order to work. In this work context, we may experience some challenges recruiting and retaining caregivers because participation in the FSI-ECD requires caregivers to attend twelve 90-minute sessions delivered once per week. Although the FSI-ECD may provide long-term benefits for caregiver mental health and child development, these benefits may not be a sufficient incentive for study participation. To help address this challenge, we will encourage highly flexible scheduling to accommodate the working hours of caregivers. The home-visiting nature of the FSI-ECD is also intended to improve service access for families with young children and will relieve the burden of traveling to attend services.

Technology literacy levels and potential technical issues that may occur with the mHealth tools could also pose challenges to this study. To address this, we will provide a 1-day technology literacy training on the use of mHealth tools and basic skills with tablet use. We will also provide ongoing technical support to troubleshoot any technical issues. It is possible that poor connectivity may impede rapid resolution of technical issues, because technical assistance will be remote. However, given that CHWs and supervisors will not need to use mHealth tools on a daily basis, our team should be capable of reasonably resolving any issues with enough time to ensure study activities proceed as planned. We will also train the study data manager in use of the mHealth tools to support greater in-country expertise. We will document any technical issues and keep a log of the strategy to resolve them in the event that the same issue is encountered on a subsequent occasion. To address potential difficulties with internet connectivity, we will place a modem for CHWs and supervisors in the peripheral health unit where they are based. Battery-powered tablets with offline functions and access to cloud storage will also ensure that mHealth tools can be feasibly used and data securely stored until connectivity is available.

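### The staff described as blinded are also the staff who assign families to arms, so the stated blinding cannot be true of them, and allocation concealment is not secured as written

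*Protocol article*

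**What the plan says.** All the statements on allocation stand in one paragraph of the protocol article, under Overview of Design.

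- **Consent:** "Study research assistants will seek informed consent from families, CHWs, and supervisors for their participation".
- **Sequence:** "The randomization allocation sequence will be generated via computer-generated random number list in REDCap".
- **Constraint on allocation:** to limit contamination, the article borrows rules from earlier work, such as "geographic information system mapping to ensure nonadjacency of control and FSI-ECD families".
- **Blinding and assignment:** "Study research assistants and data analysts will be blinded to participant assignment". The same sentence continues with the same subject, so these staff "will be blinded to participant assignment and will assign participants to study condition based on the randomization allocation sequence".

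Under FSI-ECD Outcomes, the collector of the outcome data is given only in the first person plural: "We will collect quantitative data on caregiver mental health and emotion regulation". The measures are caregiver scales and two observational instruments. For the latter, "we will use the Home Observation for Measurement of the Environment", together with an observation of mother–child interaction.

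No section names a separate person who holds the sequence, releases allocations or assigns families, and none describes coded arms. A study data manager appears once, under Possible Challenges, in connection with technical support: "We will also train the study data manager in use of the mHealth tools".

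**The concern.** The sentence gives one group of people two roles that exclude each other. Anyone who allocates a family to the home-visiting programme or to standard care has learned that family's arm by doing so.

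Two protections are at stake.

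- **Blinding after randomisation.** Families and CHWs cannot be masked to twelve weekly home sessions set against standard visits. Blinded research assistants and analysts are all the blinding the article offers. Symptom, conflict and emotion-regulation scales and ratings of the home are open to the expectations of whoever collects them.
- **Concealment before randomisation.** Research assistants seek consent and, as written, also assign. If they could see the next allocation before a family's enrolment was settled, that knowledge could influence who is enrolled. Analysis by intention to treat would not remove the resulting imbalance.

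The trial is a pilot, but preliminary effects on caregiver outcomes are among its stated aims. A bias built in at allocation or assessment cannot be repaired afterwards.

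**Working it through.** **Step 1: roles side by side (Overview of Design, FSI-ECD Outcomes).**

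| Task | Who, according to the article |
|---|---|
| Seeks consent | Research assistants |
| Generates the sequence | Computer list in REDCap; holder not named |
| Applies the nonadjacency rule | Not named |
| Assigns families to arms | Research assistants and data analysts |
| Is blinded to assignment | Research assistants and data analysts |
| Collects outcomes | Not named ("we") |

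Rows four and five name the same people, and knowing the arm follows from assigning it. This contradiction needs no figure and no inference.

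**Step 2: concealment.** Rows one and four share the research assistants, so nothing in the text separates enrolment from allocation. Whether concealment fails depends on when an allocation becomes visible, and the article does not say. The nonadjacency rule adds a difficulty: whoever applies it must know the arms of nearby families, so a family's location can carry information about its arm.

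**Step 3: what a bias would do (illustration only).** The article states no bias, so 0.1, 0.2 and 0.3 SD are assumptions.

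*Reproducing the plan's precision.* The inputs, from Data Analysis, are 80 families, 2 respondents, 2 time points, within-family correlation about 0.5, α = 0.05 and power 0.80.

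- Observations: 80 × 2 × 2 = 320.
- Design effect: 1 + (4 − 1) × 0.5 = 2.5.
- Effective n: 320 / 2.5 = 128.
- SE of the arm difference, in SD units, with equal arms: 2/√128 = 0.177.
- Detectable effect: (1.96 + 0.84) × 0.177 = 0.495, in agreement with the stated value of about 0.50.

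For outcomes with one observation per time point, the article states about 0.6. Working back from that figure, SE = 0.6 / 2.80 = 0.214.

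*Error rate under a bias b when there is no true effect:* P(|Z + b/SE| > 1.96).

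| Assumed bias (SD) | SE 0.177 | SE 0.214 |
|---|---|---|
| 0 | 5% | 5% |
| 0.1 | 8.7% | 7.5% |
| 0.2 | 20.5% | 15.4% |
| 0.3 | 39.6% | 28.8% |

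Using 0.50 / 2.80 = 0.179 in place of 0.177 changes the last entry of the first SE column only to 39.0%.

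**The case against.** The strongest defence is that the sentence is loosely compressed. It may mean that research assistants do not know the coming allocation and reveal it in REDCap once a family is enrolled. That would preserve concealment. It would not rescue the blinding claim, because the research assistants would know the arm from then on, and because the sentence includes data analysts, whose blinding has a purpose only after allocation.

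A second defence is that an article may leave to the full protocol who holds the list and when allocations are released. That is fair for those details taken alone. It does not excuse a statement of roles that conflicts with itself.

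Three stronger readings are tempting, and the article does not support them.

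- **That concealment has failed or cannot hold.** The article does not say that research assistants can read the list, nor that families are allocated one at a time. Its timeline puts enrolment and baseline in the quarter before implementation starts. Together with a rule based on location, this is compatible with allocating after all families are enrolled, when steering by the sequence would largely disappear.
- **That research assistants interview families and rate the observations.** This is a natural inference, since the text chose to blind them, and verbal consent because of low literacy makes interviewing likely. Neither is stated.
- **That the trial's error rate is 40%.** The figure needs an assumed bias of 0.3 SD and the two-respondent precision. The article also says the pilot lacks power for clinically significant effects, so the realistic harm is a biased preliminary estimate and not a failed confirmatory test.

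**Conclusion.** The point stands as an internal contradiction, and the sentence must be corrected. The people named as blinded are the people named as assigning, so the blinding claim is false of them on any reading in which they do assign. This rests on the text alone.

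Allocation concealment is unsecured, not shown to be absent. It depends on release timing and visibility that the article does not describe.

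Assessor bias in the caregiver-reported and observational outcomes is a consequence only if research assistants collect them. Its size is unknown. The ranges of about 9% to 40% and about 7.5% to 29% show sensitivity to assumed biases of 0.1 to 0.3 SD. They do not estimate what this trial would suffer, and the verdict does not depend on them.

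**What to change.** Rewrite the sentence so that each role is separate.

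1. **Allocator.** Name an existing staff member who does not enrol, assess or analyse. The study data manager is a candidate if independent of those tasks, which the article does not show and the sponsor should confirm.
2. **Timing.** State that this person applies the REDCap sequence and the nonadjacency rule only after consent and baseline are complete. Both belong in the same hands, because the rule cannot be applied without knowing the arms of neighbouring families.
3. **Disclosure.** State that the allocation goes only to the delivery side (supervisors and CHWs) and to the family.
4. **Blinding.** Limit the claim to outcome assessors and analysts who take no part in assignment, and say who the assessors are.
5. **Access.** Set REDCap user rights so that the sequence and the arm field are hidden from those assessors and analysts.

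The cost is protocol wording and some access set-up. If the data manager proves not to be independent, another person must be designated. The article reports that baseline data collection had not begun at submission, so at that stage the change could be made before any family was allocated.
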